# Effectiveness of a ‘Workshop on Decluttering and Organising’ programme for teens and middle-aged adults with difficulty decluttering: a study protocol of an open-label, randomised, parallel-group, superiority trial in Japan

**DOI:** 10.1136/bmjopen-2016-014687

**Published:** 2017-06-10

**Keywords:** Saving Inventory–Revised, Workshop on Decluttering and Organizing, Study protocol, Randomized controlled trial, Teens and middle-aged adults, Effectiveness

## Abstract

**Introduction:**

Hoarding disorder can cause problems with work performance, personal hygiene, health and well-being. The disorder is a growing social problem in Japan. Having difficulty discarding rubbish, decluttering and organising can signal a future hoarding disorder, and early intervention is important. We developed an educational workshop on decluttering and organising for teens and adults with difficulty organising. The objective of this study is to evaluate the effectiveness of a workshop for reducing clutter and improving quality of life among younger people with difficulty decluttering and organising.

**Methods and analysis:**

An open-label, parallel-group, randomised controlled trial will be conducted among volunteers aged 12–55 years with mild difficulty decluttering and organising. Those in the intervention group will attend the workshop and receive a visit from a professional cleaning company to declutter their living space. The control group will have only the latter. The primary outcome will be the score on the Japanese version of the Saving Inventory-Revised. Secondary outcomes will be scores on the Clutter Image Rating Scale, the Japanese version of the Rosenberg Self-Esteem Scale and the Roles of Private Space Scale. The results will be examined for differences between the two groups in changes from baseline to 7 months. We will examine crude effects and adjust for gender and age using a general linear model for continuous variables and a logistic regression model for dichotomous variables. Sample size was calculated assuming a significance level of 5% (two tailed), a power of 80% and an effect size of 0.75. In total, 60 subjects (30 in each group) will be required.

**Ethics and dissemination:**

The study protocol has been approved by the Medical Ethical Committee of Teikyo University (No. 15-065). The findings will be disseminated widely through peer-reviewed publication and conference presentations.

**Trial registration number:**

UMIN000020568. Issue date: 16 January 2016.

Strengths and limitations of this studyThe study will be an open-label, parallel-group, randomised controlled trial and, to our knowledge, is the first such study on this subject in Japan.The study will test a simple but feasible intervention for those with difficulty decluttering and organising.The outcomes measures are clearly set using reliable scales.The test is adequately powered to detect effects on the outcomes.Blinding is not possible because of the type of intervention, which may affect the results.

## Introduction

Having a hoarding disorder can cause problems with work performance, personal hygiene, health and well-being. Such disorders occasionally result in individuals living in environments with large amounts of garbage. Key symptoms of hoarding include difficulty discarding, excessive clutter and excessive acquisition of objects.^1 2^ The latter symptoms pose a number of dangers, such as the potential for fire and tripping over clutter. The presence of trash or clutter in one’s living space also affects an individual’s overall quality of life.^3^ This issue is a growing social problem in Japan.^4^

An individual living in such conditions can become isolated from the rest of society; this can be particularly true for older people.^5^ Unsanitary living conditions can eventually become a public health problem if they affect one’s neighbours. Hoarding disorder is therefore an individual problem and a problem for society, and a practical solution is warranted from a public health point of view.

Hoarding disorder is often accompanied by psychiatric disorders such as attention deficit hyperactivity disorder (ADHD), depression or obsessive–compulsive disorder (OCD).^6–11^ A relationship between hoarding disorder and distress tolerance and anxiety sensitivity has also been noted in a sample of young adults.^12^ Signs of hoarding were separately reported in children aged 13^13^ and 11–15 years,^14^ and the severity of the disorder evidently increases with age. Many sufferers report symptom onset before age 20 years,^14^ with symptoms tending to worsen past age 55 years.^13^ This suggests that prevention among younger people is important. To accommodate this, we targeted a wide range of participants aged 12–55 years old.

A previous study in England and Germany estimated that incidence of hoarding disorder was 1.5%–5.8%.^15 16^ Another study reported that cognitive–behavioural therapy, either individually or in groups, as well as home visits, are effective at assisting patients with hoarding disorder. However, these cognitive–behavioural therapies required relatively long intervention periods, and the subject samples were middle-aged and elderly people.^17–19^

To the contrary, a study on the effects of a brief anxiety sensitivity reduction intervention on obsessive–compulsive (OC) spectrum symptoms in a young adult sample showed reduced OC symptoms across the postintervention follow-up period. However, the intervention did not show a specific effect on reducing hoarding symptoms.^12^ There is a clear need to identify new avenues through which to develop additional interventions.

Japan’s population is ageing at an increasingly rapid rate. Given the association with age, early intervention is imperative. There is urgent need to establish a system to help prevent younger people who show signs of difficulty decluttering and organising from developing a hoarding disorder.

A previous study in Japan examined the state of the living space of 450 undergraduates from two universities.^20^ The results showed that younger people who had difficulty decluttering and organising tended to live in cluttered or disorganised living spaces and to have low self-esteem. The study used the Japanese version of the Saving Inventory-Revised (SI-R).^21^ This was developed in the USA^2^ and translated into Japanese, and its reliability and validity have been verified.^2^ The previous study’s SI-R scores had a mean of 32.1 points (±13.0) and a normal distribution. SI-R scores have been reported to be high in people who said that they did not like to clean, but many such people also want to improve the state of their living space.^20^ There are various ways to learn how to clean effectively in Japan, including workshops, books and professional support, but it is not clear which method is most effective.

We have therefore developed an education programme, of a series of workshops on decluttering and organising, for teens and adults who find it difficult to organise. In the workshops, we will help identify what belongings a person truly needs. It also covers the state of the individual’s living space and its relationship with physical and mental health. The purpose of the workshop is to improve recognition of the importance of cleaning and to change behaviour.

This study examines behaviour 7 months after the intervention, using a control group, and is designed to assess both changes in habits and levels of stress. It is impossible to blind this type of intervention, so the study was made open label to minimise bias.

The aim of the study is to evaluate the effectiveness of the programme in reducing clutter and improving the quality of life in teens and middle-aged adults who have difficulty decluttering and organising and have a cluttered living space.

**Figure 1 F1:**
[figure not shown]
Trial design.

### Participants

The study will look for volunteers aged between 12 and 55 years and who have mild organisation difficulties. Volunteers will need to meet all inclusion criteria below and not meet any of the exclusion criteria (see box 1).Box 1Inclusion criteria and exclusion criteria
*Inclusion criteria*
Individuals who have difficulty decluttering and organising. (SI-R score≥30).Individuals with a total score of four points or more on the Japanese version of the Clutter Image Rating (CIR) scale*.Individuals who are responsible for decluttering and organising their own rooms.Individuals with no planned relocations, extensive renovations of living space or room changes (to allow comparison of the state of living spaces before and after the intervention).Individuals who are able to attend at least three workshop sessions and receive visits from an organising and cleaning service.Individuals who responded in the questionnaire, ‘I want to organise my room according to my will’.Individuals who can send photographs of their living spaces at the specified time, that is, without delay.Individuals or a roommate/family member (the informed consent form for minors if the individual is under the age of 15 years) who consent in writing to their participation in the study and to having a better organised and tidied living space. If the individual is a minor, consent must be provided by a guardian.Individuals between the ages of 12 and 55 years at the start of the study.
***Exclusion criteria***
Individuals who are unable to organise and tidy up their living spaces during the study period, for example:individuals with an illness or disabilityindividuals who are not living at the registered residence or are physically unable to regularly organise and tidy up.Individuals living in a space that is too messy (an organisation expert and two cleaning experts judge the space and deem whether it can be sufficiently organised within about 3 hours).Individuals who harass other attendees while attending the workshop or who are deemed incapable of obeying the specified rules of attendance.Individuals who are rendered incapable of participation during this study.Individuals suffering from a condition or disability that is deemed to preclude study participation. If there are difficulties with that determination, an individual may be barred from participation at the discretion of a physician.Individuals who are otherwise deemed ineligible by an investigator (or subinvestigator).*The CIR Scale score for the general public is a mean of 3.8 points (±1)^20^ so the subjects in this study must have at least that score.SI-R, Saving Inventory-Revised.

### Recruitment and allocation

#### Subject recruitment

We will recruit participants in several ways, including through posters put up in visiting nursing stations, visiting care stations, community pharmacies and at a university, high school and junior high school in northwest Tokyo. We will also recruit online using a homepage, blog and social media for an events corporation, an association of organisers and a non-profit organisation that provides support for people with ADHD.

### Subject assignment

Applicants will visit Teikyo University to receive an explanation of the study objectives. After assessment via questionnaire, those verified as eligible will be immediately enrolled if they give their full consent. Each subject will then be randomly assigned to either the intervention or control group. Enrolment will continue until the required sample size (30 participants per group) is reached. We consider that the effects of lifestyle education need several months to show progress; many studies use 6 months or longer.^22 23^ We therefore set a term of 7 months by considering 6 months after the intervention begins as the observation period in the present study.

### Randomisation and blinding

A sealed envelope method will be used for random allocation. This is based on a permuted block method, with a block size of 4 and a random number table created before the study begins. Each presealed envelope, prepared by a person independent from the research, will contain a random number. Participants will open this at the location of the session meeting where they gave consent and cannot change their designated group.

Because of the open-label design, participants will know whether they are assigned to the intervention or control group. However, this information is blinded for the professional organising and cleaning service in order to avoid risk of bias.

Effectiveness of the intervention will be determined via surveys completed by the participants and sent directly to the study chair at Teikyo University along with a photograph of the room to assess the present level of cleanliness or clutter. The organising and cleaning services will not be able to see the results for individual subjects.

### Interventions

#### Intervention group

This group will attend a workshop programme, undergo inspections of cleanliness or clutter of their rooms and receive visits from an organising and cleaning service. The workshop will consist of four sessions. Room cleanliness or clutter will be inspected six times. The first inspection will take place once eligibility is verified and consent is obtained. The second will take place before the start of the study. Others will take place 4 weeks, 2 months, 4 months and 7 months after the start of the study (see figure 1).

#### Control group

The control group will receive an initial inspection to evaluate room cleanliness or clutter once eligibility is verified and consent obtained. The second inspection will take place before the intervention group starts the workshop. The control group will receive a visit from a professional cleaning company only to declutter the living spaces. Further inspections will take place 4 weeks, 2 months, 4 months and 7 months after the start of the study. Members of the control group who wish to attend the workshop may do so after the study period ends.

Additionally, until the end of the research period 7 months after commencement of the study, no participants are allowed to directly request any cleaning service be done.

### The content of the workshop

The workshop’s purpose is to improve participant behaviour and develop habits of decluttering and organising. The workshop starts by covering the relationship between physical and mental health and the state of the living space and then discusses the participants’ ideal life. A study representative has developed a workshop programme based on material from the Japan Association of Life Organizers and Edison Club, a non-profit organisation supporting patients with ADHD, their families and teachers. The textbook used in the workshop is based on a text used in elementary schools^24^; therefore, 12-year-olds should have no difficulty understanding the contents.

A public health nurse and an organiser will deliver four lectures, with the former leading the first 30 min of each lecture and the latter the final 1.5 hours (see table 1 for details).

**Table 1 T1:** Syllabus for ‘Workshop on Decluttering and Organising’

1st (2_hours)	<Reduce> Orientation and goal setting (public health nurse). Understanding the importance of working as a group (public health nurse). Three fundamentals for healthy and comfortable living (reduce, organise and maintain) (organiser). Organising in small steps: around your desk and your bed (organiser). Explanation of homework (public health nurse).
2nd (2_hours)	<Organise> Review of previous session (public health nurse). The relation between decluttering and organising and health (fall prevention and allergic disease) (public health nurse). Organising in small steps: the kitchen (organiser). Explanation of homework (public health nurse).
3rd (2_hours)	<Review> Review of previous session (public health nurse). Solutions for people who have difficulty discarding things and buy (or receive) unnecessary things (public health nurse). Organising in small steps: a place to relax (organiser). Explanation of homework (public health nurse).
4th (2_hours)	<Maintain> Review of previous session (public health nurse). Organising in small steps: closets and wardrobes (organiser). Schedule of questionnaire submission (public health nurse).

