### Statistical analysis

#### Sample size

A previous study divided 46 patients with a hoarding disorder (mean age: 53.9 years) into two groups. One group of 23 subjects was scheduled for 26 sessions of cognitive–behavioural therapy approximately on a weekly basis. The second group of 23 subjects had yet to undergo cognitive–behavioural therapy.^19^ A comparison of the two groups indicated that subjects who had completed the 12th session of cognitive–behavioural therapy had a 10-point drop in their SI-R score. Around 10 points were improved on using a pre-test on the general population. A meta-analysis in another study indicated that intervention was more effective in younger individuals than older ones. This study therefore assumed a potential 10-point improvement in SI-R score.^19^ Previous results indicated that the SI-R score had a normal distribution and SD was 13.0.^20^ The sample size was therefore calculated as 28 per group under the assumptions of a significance level of 5% (two tailed), a power of 80% and an effect size of 0.75. Considering the likely dropout rate, we set the sample size needed for this trial as 60 subjects in total, 30 in each group.

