#### Statistical analysis

Analyses will be conducted under the intention-to-treat principle. The main target set for analysis is the full analysis set. Missing data will be permutated under the assumption of missing at random following the last observation carried forward principle. A sensitivity analysis will be performed using the multiple imputation method. The secondary target set for the analyses will be the per-protocol set.

Summary statistics (maximum, median, minimum, mean and SD) will be calculated for all continuous data, and frequency and proportion for categorical data.

The differences in effect sizes between the two groups will be examined using a t-test. Differences will be assessed in a general linear model by adjusting for gender, age and marital status at the start of the study and outcome measure at the baseline. Crude and adjusted ORs will be calculated for binary variables and the two groups will be compared using logistic regression analysis. As secondary analysis, mixed-effects random-effects models will be used as a longitudinal data analysis. The significance level for testing will be set at p<0.05 (two tailed).

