### Timeframe of the study

Participants were registered between January and May 2016. Eight workshops have been run between 3 February and 11 June 2016. Data are currently being collected.

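### The t-test, adjusted models and sample size ignore group delivery of the workshop in one arm, so the precision of the workshop effect may be overstated

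*Protocol article*

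**What the plan says.** **Allocation and delivery.** Participants are randomised individually in permuted blocks of 4 (Subject assignment; Randomisation and blinding). The intervention arm attends a four-session workshop and also receives the cleaning visit. The control arm receives the visit only and may take the workshop after the study period (Interventions). The workshop is attended with others: session 1 in Table 1 includes "Understanding the importance of working as a group", and an exclusion criterion in Box 1 concerns people who harass fellow attendees.

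**Number of groups.** The only information is under Timeframe of the study: "Eight workshops have been run between 3 February and 11 June 2016". Neither the number nor the size of the groups is given.

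**Analysis.** Under Statistical analysis: "The differences in effect sizes between the two groups will be examined using a t-test". A general linear model follows, adjusted for gender, age, marital status and the baseline value, with logistic regression for binary variables. None of these has a term for workshop group. A mixed-effects model is named as a secondary longitudinal analysis, without its random effects.

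**Sample size.** "The sample size was therefore calculated as 28 per group", on the assumptions of a "significance level of 5% (two tailed), a power of 80% and an effect size of 0.75". The total is then set at 60, with the increase from 28 to 30 per group attributed to dropout. The strengths and limitations list states that power is sufficient.

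**The concern.** People who share sessions and group work may end up more alike at 7 months than people who did not. Here that can happen in one arm only, which makes the design partially nested: intervention participants sit within workshop groups, and controls stand alone.

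A two-sample t-test, or a linear model without a group term, then counts each intervention participant as a full independent unit. If the within-group correlation is positive, the standard error is too small, the interval too narrow and a claim of effectiveness too easy. With very few groups, how one or two of them happened to go could be read as an effect of the programme. This matters because the Discussion plans to publicise the workshop widely for others to run if it is found effective. The inference wanted is about the workshop in general, not about these particular groups.

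**Working it through.** **1. Reproduce the plan's figure.** Inputs from Sample size: two-sided alpha 0.05, power 80%, standardised effect d = 0.75. (The stated 10 points and SD 13.0 give 10/13 = 0.769; the plan uses 0.75.)

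n per arm = 2 × (1.96 + 0.8416)² / 0.75² = 2 × 7.849 / 0.5625 = 27.9, so 28.

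The plan's 28 is reproduced, for independent observations with no design effect. Power at 30 per arm is Φ(0.75/√(2/30) − 1.96) = Φ(2.905 − 1.96) = 83% (81.5% with the exact t distribution).

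**2. Possible group sizes (assumption).** There are four sessions per programme. If the eight workshops are single sessions, 8/4 = 2 groups of 15. If they are eight full programmes, 30 people make six groups of 4 and two of 3.

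**3. ICC (assumption).** The documents give none. The range used is 0.01 to 0.10.

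**4. Formulas.** Total variance is set to 1 in both arms, with 30 per arm.
- Size-weighted group size: m = Σmⱼ²/30, which is 15 for two groups and (6×16 + 2×9)/30 = 3.8 for eight.
- Design effect in the workshop arm: DE = 1 + (m − 1) × ICC.
- True SE over naive SE: f = √((1 + DE)/2).
- Actual two-sided alpha: 2 × (1 − Φ(1.96/f)).
- Power on the correct SE: Φ(2.905/f − 1.96).
- n per arm for 80% power at that group size: (1 + DE) × 7.849/0.5625.

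**5. Results.**

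| Groups | ICC | DE | f | Actual alpha | Power | n per arm |
|---|---|---|---|---|---|---|
| any | 0 | 1.00 | 1.00 | 5.0% | 83% | 28 |
| 2 of 15 | 0.01 | 1.14 | 1.03 | 5.8% | 80% | 30 |
| 2 of 15 | 0.05 | 1.70 | 1.16 | 9.2% | 71% | 38 |
| 2 of 15 | 0.10 | 2.40 | 1.30 | 13.3% | 61% | 48 |
| 8 of about 4 | 0.01 | 1.03 | 1.01 | 5.2% | 82% | 29 |
| 8 of about 4 | 0.05 | 1.14 | 1.03 | 5.8% | 80% | 30 |
| 8 of about 4 | 0.10 | 1.28 | 1.07 | 6.6% | 78% | 32 |

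Simulating the planned t-test (40,000 runs per row) gave alpha of 6.0%, 9.1% and 13.5% for two groups, and 5.1%, 5.8% and 6.6% for eight.

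**6. In SI-R points.** With the plan's SD of 13.0, the naive SE is 13.0 × √(2/30) = 3.36 and the 95% half-width is 1.96 × 3.36 = 6.6. With two groups of 15, multiplying by f gives 6.8, 7.6 and 8.6 at ICC 0.01, 0.05 and 0.10.

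**7. Can the group variance be estimated?** A test with Satterthwaite degrees of freedom based on two groups has about 4 df and 58% power even at ICC 0, falling to 2 df and 25% power at ICC 0.10. With eight groups it has about 23 to 19 df and 79% to 74% power.

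**The case against.** The case on the other side is substantial.

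- **Nothing shows that the ICC is positive.** A reader might infer that the standard error is definitely too small. The documents do not support that: at ICC 0 the planned analysis is correct, and they give neither an ICC nor group sizes. This stands, and the point has to be conditional.
- **The type I error depends on the null.** If the workshop changes nobody, attending it creates no correlation in one arm, and individual randomisation protects the t-test. The inflated rates apply to a null in which particular groups do shift outcomes, up or down, but the shifts average to zero over the groups that might have been run. This stands as a limit on the claim. That is still the relevant null if the result is to be carried to new groups.
- **Not every planned analysis is shown to ignore groups.** The random effects of the secondary longitudinal model are not stated and may be left to an analysis plan not shown here. This stands. The t-test, the listed covariates and the sample size are fixed in the article.
- **Evidence of strong clustering is thin.** Sessions are described as lectures, much of the content concerns each person's own rooms, and group work is a single syllabus item. Leaders who are the same in every round add nothing to between-round variance. This argues for a small ICC, not for zero.
- **Closed groups are not stated.** Box 1 asks for ability to attend at least three sessions, and registration overlapped with the workshops, so people may have mixed sessions. This stands, and is a reason to record actual membership before choosing a model.

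**Conclusion.** The point holds in conditional form. The workshop is attended in groups in one arm only, while the t-test, the adjusted linear model, the logistic regression and the sample size assume independent participants. Any positive within-group correlation then makes the standard error too small for an effect generalised beyond the groups run.

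The size cannot be fixed from the article. It ranges from close to negligible (eight small groups) to material (two groups of 15 with an ICC of 0.05 or more). The highest figure, 13.3%, needs both the two-group reading and the top of an assumed ICC range, and should not be quoted as the trial's error rate. Nor is the 28 per group an arithmetic error: it is right for the independence it assumes. But the two extra participants per arm are already assigned to dropout, so little is left to absorb clustering.

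**What to change.** 1. Record each intervention participant's workshop group, and state the number and size of groups and whether people moved between them.
2. Before the results are seen, pre-specify a sensitivity analysis of the primary endpoint. Report the confidence interval for the 7-month difference in SI-R change with the workshop-arm variance multiplied by 1 + (m − 1) × ICC, at fixed ICCs such as 0.01, 0.05 and 0.10, where m is the size-weighted mean group size.
3. Fit a partially nested model (random group effect in the intervention arm only, controls as singletons, small-sample degrees of freedom) only if there are enough groups to estimate the variance. With two groups there are not.
4. Qualify the statement on power as assuming no clustering by workshop group.

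A claim of success should not be tied to surviving one chosen ICC, because no value has a source in the documents. The intervals should be shown and the reader left to judge.

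**Cost.** A short addition to the analysis plan, one variable per intervention participant, and a wider interval in the sensitivity analysis. The article reports registration and the workshops as finished, so the sample size is not at issue now. It also says that data are still being collected, so the analysis can still be specified in advance. The documents do not mention attendance records; if none were kept, membership would have to be reconstructed.
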